## Abstract

**Background:** People with severe mental disorders (SMDs) have higher disease and death rates than the general population. Stigma (negative attitudes and perceptions) contributes to limited access to health services and a lower quality of medical assistance in this population, and it is manifested as negative attitudes, social distance, and discrimination toward this social group. For these reasons, healthcare workers are a priority group for anti-stigma interventions. This study aims to assess the effectiveness of a program specifically designed to decrease negative attitudes and social distance and increase inclusive behaviors in healthcare workers toward people with SMD.

**Methods:** The study will be a randomized clinical trial. A minimum of 210 healthcare workers from 11 primary care centers in the province of Concepción, Chile, will be randomly chosen to receive the program or be part of the control group. There will be a pre-, post-, and 4-months evaluation of social distance, attitudes, and behaviors of participants toward people with SMD using standardized scales such as the social distance scale, which is a scale of clinician attitude toward mental illness adapted from attitudes of clinicians toward mental illness, and self-reports. The intervention program will consist of education strategies, direct, and indirect contact with people diagnosed with SMD, and skill development. There will be six face-to-face sessions directly with the participants and two additional sessions with the directors of each healthcare center. The program will involve a facilitator who will be a healthcare professional and a co-facilitator who will be a person diagnosed with SMD.

**Discussion:** This study will evaluate an intervention program especially designed to reduce stigma in healthcare workers toward people with SMD, a topic on which there is little background information, particularly in low- and middle-income countries. It is important to have interventions with proven effectiveness for this purpose to ensure equity in healthcare services.

**Trial Registration:** This study was registered under ISRCTN.com (ISRCTN46464036).

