### Procedure

Primary healthcare centers from the province of Concepcion, Chile will be invited to participate. The participation of each center is approved by the Ethical-Scientific Committee of each health service and authorized by their directors. A requirement for the inclusion of a center in the study is the authorization for the participation of health workers in the program sessions during work hours. Various activities will be performed to promote the program in each selected health center and to encourage participation. The program will be implemented in health centers where there are at least 18 people enrolled to permit the randomization of control and experimental groups with at least nine people per group. Given the sizes of the centers, a maximum number of 40 participants will be considered per health center since it is unlikely that there will be more than that number of people enrolled. The randomization process will form groups with 9 to 20 people. All healthcare workers will be invited to participate through informative meetings and flyers distributed in each health center. Once the participants have agreed to take part in the program and have been evaluated, they will be randomized. The initial evaluation (T1) will take 3 weeks, and the implementation of the program will last a total of 8 weeks. The post-test evaluation (T2) will be done during the 3 weeks following the end of the program. Four months after the end of the program, the follow-up evaluation will be performed (T3) (Table 1).

**Table 1 T1:** Study assessment points.

**Measurement**	**Scale**	**T1**	**T2**	**T3**

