**STIGMA IN PRIMARY HEALTHCARE WORKERS TOWARD PEOPLE WITH DIAGNOSIS OF SEVERE MENTAL DISORDERS (SMD)**				
Attitudes of the general public toward people with SMD	Community Attitudes to Mental Illness (CAMI) scale	✔	✔	✔
Attitudes of professionals and students working in health toward people with SMD	Mental Illness: Clinicians' Attitudes (MICA) scale	✔	✔	✔
Social distance that people have toward people with SMD	Social distance scale (SD)	✔	✔	✔
Self-perception of behaviors that one had toward the last person diagnosed with SMD with whom they had contact	Self-registration of inclusive behaviors	✔	✔	✔

*T1, assessment before intervention; T2, assessment after intervention; T3, follow-up 4 months after assessment T2*.

Workers assigned to the control group will receive the program once the implementation is completed and the post and follow-up evaluations are finished. A minimum of 11 centers are needed to obtain the required sample size (Table 1).

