### Power and Data Analyses

An experimental multilevel mixed effects design with effects between groups (treatment vs. control) and within groups (time), with pre- and post-test measurements and with a four-month follow-up, will be used. Estimation of the effect will be by intention-to-treat. To estimate the effect of the intervention on post-test measurements, it should be taken into account that there are multiple outcomes and the results per person are not independent of each other but can have distinct distributions. Therefore, a multivariate analysis of covariance (MANCOVA) will be used where the presence of clustering per healthcare center is considered as a factor, while the pre-test measurement and previous contact with someone with SMD are considered as co-variables. Previous verification of the assumptions that the model provides, i.e., presence of normal multivariate distribution of the transformation of the measurements, as well as homogeneity of the variance/covariance matrix between the groups under study, is necessary.

Once it has been determined that the intervention is successful in general terms, specific analyses of each result will be performed using mixed ANCOVA that considers participation in the control group or experimental group as a fixed factor of interest, pre-measurement as a co-variable, and enrollment in the primary healthcare center as a random factor. To detect a moderate effect for the intervention (*d* = 0.5) with a power of 95% and a level of significance of 5%, a minimum sample of 105 participants per group is estimated (210 participants in total). This number was obtained by performing a simulation procedure using a mixed ANOVA considering the existence of a significant interaction effect between moment X group experimental/control. Considering a 10% loss in percentage, 231 is the minimum estimated number of participants.

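### The recruitment minimum is given as 210 in the Abstract and 231 in the power section, and 231 is slightly too few to leave 210 after a 10% loss (minor)

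*Protocol article*

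**What the plan says.** Four places in the protocol article bear on the recruitment minimum.

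- **Power and Data Analyses, base figure.** For d = 0.5, power 95% and significance level 5%, the text says "a minimum sample of 105 participants per group is estimated (210 participants in total". It attributes this number to a simulation using a mixed ANOVA with a time-by-group interaction.
- **Power and Data Analyses, after loss.** "Considering a 10% loss in percentage, 231 is the minimum estimated number of participants".
- **Abstract, Methods.** "A minimum of 210 healthcare workers from 11 primary care centers". These workers are the ones to be allocated at random to program or control, so 210 is a number randomised here. No loss is mentioned.
- **Procedure.** A centre takes part if it has "at least 18 people enrolled to permit the randomization of control and experimental groups with at least nine people per group", and no centre is expected to exceed 40. After Table 1 the text adds: "A minimum of 11 centers are needed to obtain the required sample size".

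**The concern.** The same number, 210, has two roles. In the power section it is what the calculation requires before any loss. In the Abstract it is the minimum to be randomised. Both 210 and 231 are called a minimum, and they cannot both be the point at which recruitment is complete.

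The allowance for loss is also computed by the wrong operation. Adding 10% to the required number does not restore it once 10% of the enlarged number is lost.

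What is at stake is the stated power. A team that worked to the Abstract would meet a published minimum and, with the loss the plan itself expects, finish below the number on which the 95% rests.

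**Working it through.** **Inputs.** From Power and Data Analyses: d = 0.5, power 0.95, significance level 0.05, 105 per group, loss 10%, inflated total 231. From the Abstract: 210 randomised, 11 centres. From Procedure: 18 to 40 participants per centre, at least 11 centres. From Design: similar numbers per arm, taken as 1:1. The article does not state sidedness; two-sided is my assumption, tested in step 1.

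**1. Reproduce the base figure.** Normal approximation, per group:

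n = 2(z₀.₉₇₅ + z₀.₉₅)²/d² = 2(1.960 + 1.645)²/0.25 = 104.0

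The t-test version gives 104.93, so 105 per group and 210 in total, as stated. A one-sided test gives 87 to 88 per group and does not match. The two-sided t-test is therefore a reasonable stand-in for the simulation, whose inputs (such as the correlation between measurements and the centre effect) are not given.

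**2. Reproduce the inflated figure.** 210 × 1.10 = 231 exactly. To have 210 left after a 10% loss:

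N = 210/(1 − 0.10) = 233.3, so 234 (117 per group)

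Check: 231 × 0.9 = 207.9, which is below 210; 234 × 0.9 = 210.6, which is not. Put another way, 231 covers a loss of 21/231 = 9.1%, not 10%. The shortfall is 3 participants, or 3/234 = 1.3%.

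**3. Power at each figure.** Two-sided two-sample t-test, d = 0.5, equal arms, with lost participants contributing nothing:

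| Randomised | Left after 10% loss | Power |
|---|---|---|
| 234 | 210.6 | 95.1% |
| 231 (power section) | 207.9 | 94.8% |
| 210 (Abstract) | 189 | 92.8% |

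With exactly 210 evaluable the power is 95.0%. The multiplication slip therefore costs about 0.2 points, and reading the Abstract's figure as the target costs about 2.2 points.

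**4. Do the centre numbers fit?** 231/11 = 21.0 per centre and 234/11 = 21.3. Both lie inside 18 to 40, so 11 centres are consistent with either total. If every centre had only 18, then 11 × 18 = 198, and 13 centres would be needed for 231 or 234 (12 × 18 = 216; 13 × 18 = 234).

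**The case against.** **The methods section governs.** The power section states a recruitment figure that allows for loss, and the Abstract only repeats the pre-loss number from the same paragraph. That is fair as to how the slip arose. It does not remove the conflict, because the Abstract attaches its figure to the workers who are randomised.

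**The inflation slip is trivial.** Three people and 0.2 points of power change no conclusion. This stands. It is a reason to grade the point as minor, not to leave a wrong figure in place.

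**The t-test is not the planned analysis.** The plan adjusts for the pre-test measurement and treats centre as a random factor. If d = 0.5 is on the unadjusted standard deviation and centre effects are ignored, 189 evaluable give 92.8% power with a pre-post correlation of 0, 94.8% with 0.3 and 97.7% with 0.5. The correlation is not given, so these figures are illustrations. What stands is that 92.8% and 94.8% in the table above are approximations from an unadjusted comparison, not the power of the planned model.

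**The centre rule.** A reader might infer that 11 centres at the permitted minimum, 198 people, contradict the sample size. The documents do not support that. Eighteen is an eligibility floor for one centre, and 11 is a minimum number of centres tied by its own sentence to reaching the required sample. The article nowhere plans 198, and a team holding 198 would have met neither 210 nor 231. What remains is only that the two floors together do not guarantee the total.

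**Conclusion.** The recruitment minimum is wrong as written, and the point is minor. The Abstract and the power section give different minimums, and the larger of the two falls 3 short of what its own loss allowance requires. With the planned 10% loss, power is about 94.8% at 231 randomised and about 92.8% at 210, against the stated 95%.

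These figures rest on a two-sided two-sample t-test at d = 0.5 with 1:1 allocation, no centre effect and no baseline adjustment. It reproduces 105 per group but is not the article's simulation.

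A reader might go further and say that the trial's power is undermined. The figures do not support that: at either stated minimum, the approximate shortfall is at most about 2 points. The 11 centres are consistent with 231 and are not themselves an error.

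**What to change.** State one recruitment minimum in the Abstract and in Power and Data Analyses: 234 randomised, to leave 210 evaluable after a 10% loss. Alternatively, keep a lower figure in both places and restate the power that goes with it, taken from the plan's own simulation; on the approximation above this is about 94.8% for 231 and 92.8% for 210.

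The sentence on centres after Table 1 could add that 11 centres assumes a mean of about 21 to 22 participants per centre, and that recruitment ends on the participant total and not on the centre count. This is a clarification and not a correction.

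The cost is three more participants than the power section now states (24 more than the Abstract's 210), or a slightly lower stated power, plus a few changed words.

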## Discussion

It is expected that an intervention program that recognizes the aforementioned aspects will reduce the stigmatization that healthcare workers have toward people with SMD. Reducing stigma toward people with SMD should be one of the priorities of a policy aimed at ensuring the rights of people with psychiatric diagnoses and guaranteeing equity in health care. The results of this study could help future research to evaluate the potential of the program to be part of a global strategy geared toward improving equity in health care and the quality of life of people with SMD and their families.

One limitation of this study is the risk of contamination between the control and experimental groups within each healthcare center. However, it was estimated that this risk was lower given the characteristics of the centers and the program, which assumes that attitudinal change is not easily achieved and that direct contact with people having SMD is decisive. This experience cannot be transmitted to other people without a substantial effort. Therefore, considering the working conditions of the healthcare personnel (high demand and overload), group crosstalk is not expected to frequently occur, thereby decreasing the possibility of contamination. Furthermore, the study design of this intervention program avoids the methodological difficulties of clustered designs, which are the preferred choice to have less risk of contamination. The results of this study will be published in scientific journals and scientific meetings, and it will also be presented to the general public, especially to those involved in protecting the rights of people with SMD, and to health authorities. The data of this study will be available to those who request it.

## Ethics Statement

This study was approved by the Scientific Ethics Committee of the corresponding Health Services and was designed taking into consideration the rights of the participants included in the Declaration of Helsinki and the principles of respect, autonomy, and beneficence. All participants (professionals and technicians) were invited to participate, and if they accepted, they were asked to express their agreement by signing an informed consent form. In the case of the members of the organization of people diagnosed with SMD, they are accustomed to participate in anti-stigma activities since it is one of the objectives of the organization. It is well documented that this type of activity improves the esteem and confidence of people with SMD and does not violate their integrity or rights; on the contrary, it favors the process of their recovery (50).
